### Interventions

2.3

#### Screening

2.3.1

If the patient assigned an elective low anterior rectal resection meets the inclusion criteria, the patient will be asked to review the informed consent form for participation in the study; a detailed explanation of the participant's obligations and rights in case of participating in the study will be provided. All interventions related to the study will be carried out only if the patient has signed the informed consent. Upon provision of the informed consent, the patient will be assigned a number of procedures aimed at assessing the patient's compliance with the eligibility criteria:

1.Sigmoidoscopy2.Tumor biopsy3.Computed tomography of the abdominal cavity and chest4.MRI of the pelvis5.Internist and anesthesiologist consults6.Oncology case conference7.Baseline assessment of the overall and cancer-specific quality of life (SF-36 and QLQ-C30 questionnaires, respectively)8.Incontinence assessment (CCIS)

Based on the results of the screening, the stage of the disease, indications and type of surgical treatment, the possibility of performing a TME, and surgical approach (laparoscopic or open) are determined.

#### Preoperative preparation

2.3.2

On the day before the surgery, mechanical bowel preparation is performed by oral administration of polyethylene glycol or sodium phosphate solution. The standard premedication regimen includes phenazepam 0.5 mg at night before bed and morning before surgery. Depending on present comorbidities, an individual regimen of preoperative examination and preparation may be selected.

#### Day of surgery

2.3.3

Under a combined general anesthesia, the patient is placed in a modified lithotomy position on the back, with legs spread apart on supports and arms along the torso. The operative field is treated with an antiseptic solution twice and draped.

##### Open approach

2.3.3.1

A midline laparotomy is performed. After an examination of the abdominal cavity and the pelvic cavity, mobilization of the sigmoid colon in the lateral-medial direction begins. Para-aortic lymph node dissection is performed and inferior mesenteric artery is skeletonized with preservation of the integrity of preaortic and prehypogastric plexuses. The inferior mesenteric artery is ligated below the origin of the left colic artery; the latter is preserved. The inferior mesenteric vein is cut at the level of the superior edge of the body of the pancreas. The mesentery of the sigmoid colon is cut in the direction of the intestinal wall. The place of the transection of the sigmoid colon is determined at a distance of at least 15 cm above the tumor in an area with an adequate blood supply. Sigmoid colon is divided and the circular stapler anvil is fixed in its stump with a purse-string suture. After that, a TME is performed with the preservation of the hypogastric nerves and pelvic nerve plexuses. L-shaped clamp is applied to the rectum at least 2 cm below the tumor. From the side of the perineum, the rectal stump is washed with an antiseptic solution. After that, below the L-shaped clamp, a linear cutter stapler is applied and the rectum is transected. The surgeon inserts the circular suturing device into the anal canal. Under the guidance of a direct observation, the trunk of the operating part of the device is pierced in the area of one of the edges of the suture line of the rectal stump. The stump of the sigmoid colon is moved to the pelvic cavity, the rod of the device anvil is put on the trunk of the operating part, and end-to-end colorectal anastomosis is formed. The height of the anastomosis is measured (in centimeter from the edge of the anal canal). After the removal of the circular suturing device, the integrity of the resected intestinal rings is checked. The suture line is tested for leakage. A transanal silicone tube is installed. A preventive transverse colostomy is formed. A silicone drain tube is installed in the pelvic cavity. The laparotomy wound is sutured. Sterile dressings are applied.

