### Trial design

1.3

THREESTAPLER study is a prospective, randomized, controlled, patient and outcomes assessor blinded, uni-center, noninferiority, parallel group, 2-arm trial with 1:1 allocation ratio. Randomization will be performed using block method after intraoperative eligibility assessment.

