### Eligibility criteria

2.2

To be eligible for randomization, an individual must comply with all of the following criteria:

Inclusion criteria

1.1.Provision of signed and dated informed consent form1.2.Stated consent to comply with all study procedures and availability for the duration of the study1.3.Male or female1.4.For females of reproductive potential: not pregnant at the time of screening1.5.For males of reproductive potential: use of condoms or other methods to ensure effective contraception with partner1.6.Histologically proven primary rectal adenocarcinoma located within 5 to 15 cm from anal verge not involving internal and/or external sphincter muscle

Exclusion criteria

2.1.Preoperative and intraoperative2.1.1.Current use of antiplatelet drugs, acetylsalicylic acid, or anticoagulants within 7 days prior to intervention2.1.2.Unresectable tumor, inability to perform a TME with colorectal anastomosis, inability to complete R0 resection, or presence of T4b tumor necessitating a multiorgan resection2.1.3.Inability to save the left colic artery2.1.4.Diameter of rectal lumen is unable to contain the working part of the stapler2.1.5.Infection requiring antibiotic treatment within 30 days prior to intervention2.1.6.Anal incontinence prior to surgery (Wexner continence grading scale ≥10)

Postoperative

2.2.1.Inability to complete all the trial procedures2.2.2.Death due to causes unrelated to anastomotic leak in early postoperative period2.2.3.Patient wants to withdraw from the clinical trial

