##### Laparoscopic approach

2.3.3.2

Following trocar installation and examination of abdominal cavity and pelvic cavities, para-aortic lymph node dissection is performed with the skeletonization of the inferior mesenteric artery and preservation of the integrity of the preaortic and prehypogastric plexuses. The inferior mesenteric artery is divided below the origin of the left colic artery; the latter is preserved. The sigmoid colon and the distal portion of the descending colon are mobilized in the medial-lateral direction. The inferior mesenteric vein is cut at the level of the upper edge of the body of the pancreas. After that, a TME is performed with the preservation of the hypogastric nerves and pelvic nerve plexuses. The rectum is transected with a linear cutter stapler at least 2 cm below the inferior margin of the tumor. A mini-laparotomy is performed. In the wound, the separated rectum and the sigmoid colon are removed, the mesentery of the sigmoid colon is transected in the direction of the transection of the intestinal wall. Sigmoid colon is divided and the circular stapler anvil is fixed in its stump with a purse-string suture. The stump of the intestine with circular suturing device anvil is immersed in the abdominal cavity, the laparotomy wound is sutured. A repeated laparoscopy is performed. From the side of the perineum, after preliminary washing of the rectal stump, the surgeon inserts the circular suturing device into the anal canal. Under guidance with a laparoscope, the trunk of the working part of the apparatus is pierced in the area on one of the edges of the suture line of the rectal stump. The sigmoid colon stump is moved to the pelvic cavity, the rod of the device head is inserted into the trunk of the operating part, an end-to-end colorectal anastomosis is secured. The height of the anastomosis is measured in centimeter from the anal verge. After the removal of the circular suturing device, the integrity of the resected intestinal rings is assured. The suture line is tested for leakage. A transanal silicone tube is installed. A preventive transverse colostomy is formed. A silicone drain tube is installed in the pelvic cavity. Abdominal wall openings are sutured. Sterile dressings are applied.

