#### Allocation

2.8.1

Participants will be randomly assigned to either control or experimental group with a 1:1 allocation ratio using fixed block randomization with a computerized random number generator. The block size equals at least 4 and will be unknown to the principal investigator, outcomes assessor and the operating surgeon. Because the possibility of making a stapled anastomosis will only be determined intraoperatively by the operating surgeon with respect to exclusion criteria precluding stapled anastomosis formation, all subjects will be allocated intraoperatively.

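### In the open operation the circular-stapler anvil is fixed before the TME, so the arm must be known while some intraoperative exclusions are still undecided, contrary to the stated rule of randomizing after eligibility is settled

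*Protocol article*

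**What the plan says.** **The rule.** Protocol article, 1.3 Trial design: "Randomization will be performed using block method after intraoperative eligibility assessment". Section 2.2 Eligibility criteria opens the list with "To be eligible for randomization, an individual must comply with all of the following criteria". Section 2.8.1 Allocation gives the reason for waiting: "the possibility of making a stapled anastomosis will only be determined intraoperatively by the operating surgeon", and therefore "all subjects will be allocated intraoperatively". No section names the surgical step at which the allocation is opened.

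**The exclusions concerned.** Under the preoperative and intraoperative heading of 2.2, item 2.1.2 begins "Unresectable tumor, inability to perform a TME with colorectal anastomosis, inability to complete R0 resection", and item 2.1.4 reads "Diameter of rectal lumen is unable to contain the working part of the stapler".

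**The open sequence.** Section 2.3.3.1: "Sigmoid colon is divided and the circular stapler anvil is fixed in its stump with a purse-string suture. After that, a TME is performed". Clamping, washout, rectal transection and transanal insertion follow. The same section later joins this anvil to the operating part of the circular device.

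**The laparoscopic sequence.** In 2.3.3.2 the TME comes first, then "The rectum is transected with a linear cutter stapler at least 2 cm below the inferior margin of the tumor". The anvil is placed only afterwards, through the mini-laparotomy.

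**Related provisions.** Blinding is claimed for the patient and the outcomes assessor (1.3). Section 2.9.3 commits to intention to treat. Section 2.2 also lists postoperative exclusions. Secondary outcome 3 in 2.4.2 counts stapler dysfunction.

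**The concern.** The two arms use circular staplers from different manufacturers, and the anvil belongs to the stapler. Once it is fixed in the colon, the surgeon knows the arm. In open cases this happens before the pelvic dissection that settles whether a TME with anastomosis can be completed, whether the resection is R0, and whether the stapler will pass. The person who then decides whether the patient is excluded already knows the device.

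Two things are at stake. First, borderline patients could be removed more readily from one arm, which would distort the leak comparison in a trial with a 5-point margin. Second, a stapler that does not pass or does not complete the join could be filed under exclusion 2.1.2 or 2.1.4. It would then disappear from both the stapler dysfunction outcome and the analysis.

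**Working it through.** **Step 1. Order of events.** No published figure is in dispute here; the check is one of sequence.

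| Item | Open (2.3.3.1) | Laparoscopic (2.3.3.2) |
|---|---|---|
| Exploration of abdomen and pelvis | before anvil | before anvil |
| Left colic artery preserved (exclusion 2.1.3) | before anvil | before anvil |
| TME | **after anvil** | before anvil |
| Rectal transection | **after anvil** | before anvil |
| Transanal insertion of the device | **after anvil** | after anvil |

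In the laparoscopic sequence allocation can follow the TME and transection. Only the actual passage of the device comes later, and that holds for any sequence. In the open sequence, completion of the TME with anastomosis, R0 and lumen fit are all unsettled when the anvil is chosen. Not every exclusion is still open then: the left colic artery question is closed, and gross unresectability or a T4b tumor may have been seen at exploration.

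**Step 2. How many patients.** The open share is not given. Assuming 20% to 60%: 0.20 × 154 = 31 and 0.60 × 154 = 92 patients, or about 15 to 46 per arm of 77.

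**Step 3. What exclusion could do (assumed inputs).** Let a fraction f of the experimental arm, with leak risk q, be dropped after the arm is known. With the centre's 18% (2.6 Sample size) as that arm's rate, the observed rate is (0.18 − f·q)/(1 − f).

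- f = 5%, q = 30%: (0.18 − 0.015)/0.95 = 17.4%, a shift of 0.6 points.
- f = 10%, q = 40%: (0.18 − 0.04)/0.90 = 15.6%, a shift of 2.4 points.
- f = 15%, q = 50%: (0.18 − 0.075)/0.85 = 12.4%, a shift of 5.6 points.

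For the error rate, put the truth at the margin (control 18%, experimental 23%), with 77 per arm before exclusion and one-sided alpha 0.05. The observed experimental rate is p = (0.23 − f·q)/(1 − f), and the chance of wrongly declaring noninferiority is Φ[(0.23 − p)/SE − 1.645], where SE² = 0.18 × 0.82/77 + p(1 − p)/(77(1 − f)).

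- f = 5%, q = 40%: p = 22.1%, type I error 6.6%.
- f = 15%, q = 50%: p = 18.2%, type I error 18.2%.

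These are fractions of a whole arm, while only open cases are exposed. With a 20% open share, f = 5% to 15% means dropping 25% to 75% of that arm's open cases (0.05/0.20 and 0.15/0.20). With a 60% share it means 8% to 25%. The upper end is therefore hard to reach when open surgery is uncommon.

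**Step 4. The opposite effect of keeping everyone.** A patient with no anastomosis cannot have an anastomotic leak. If 4 of 77 in one arm (assumption) have none and count as non-leaks, 18% reads 18% × 73/77 = 17.1%, and 23% reads 23% × 73/77 = 21.8%. If it happens equally in both arms, a true 5-point difference shrinks to 5 × 73/77 = 4.7 points. Retention thus brings a smaller distortion of its own, in the direction of noninferiority.

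**The case against.** The strongest reply is that the text already protects the comparison. Screening (2.3.1) determines from imaging and the case conference whether a TME is possible. The open procedure begins with exploration. The criteria are framed as conditions for randomization, so they should not operate afterwards, and 2.9.3 specifies intention to treat. A surgeon could judge eligibility at exploration and allocate then. This is also a condensed article, and the exact moment of allocation may be stated elsewhere.

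Part of this stands. The bias arises only if allocated patients are dropped, and the article does not say outright that they will be. But a screening judgement is provisional: 2.8.1 itself says the matter can be settled only during surgery. Intention to treat stands beside intraoperative and postoperative exclusions in 2.2 that permit removal of patients. And the conflict is between statements the article does print, so it is not a matter of omitted detail.

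Three stronger readings are tempting but unsupported:

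- *Allocation concealment is broken in open cases.* Concealment concerns foreknowledge before assignment. The sequence is computer-generated and the block size is withheld from the surgeon; the anvil step changes neither. The issue is exclusion after allocation.
- *The surgeon's knowledge during the TME contradicts the blinding.* Blinding of the surgeon is never claimed.
- *The effect is close to the whole margin.* Removing four would-be leaks from one arm turns 14/77 (18.2%) into 10/73 (13.7%), a 4.5-point shift. Nothing in the documents supports that number. At a 20% open share, one arm has about 15 open cases and 0.18 × 15.4 = 2.8 expected leaks, fewer than the four removed. Patients excluded because no anastomosis could be made were not going to leak.

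It is also fair to note that both staplers carry the size designation 29, which weakens the idea that lumen fit differs by arm. The article does not give the dimensions of the working parts.

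**Conclusion.** The contradiction holds for open cases. The rule in 1.3, 2.2 and 2.8.1 cannot be met by the order in 2.3.3.1 for feasibility of TME and anastomosis, R0 and lumen fit, provided the anvils are device-specific. The documents do not say so, but different manufacturers and the joining of anvil to operating part make it likely. The laparoscopic order does not raise the same conflict.

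The consequence is a route to arm-aware exclusion after allocation, not a demonstrated bias. Its size cannot be derived, because neither the open share nor the frequency of late exclusions is given. The 0.6 to 5.6 points and the 6.6% to 18.2% type I error are illustrations under assumed inputs, and they apply only if excluded patients leave the analysis. Severity is moderate: the defect affects an unknown share of patients and is cheap to close, but it is hard to repair later if excluded patients are not followed.

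**What to change.** Reconcile 1.3, 2.2, 2.3.3.1, 2.3.3.2 and 2.8.1. Which surgical order is used is for the sponsor and is not prescribed here. The text should:

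1. Name the point at which allocation is opened in each approach, relative to the anvil step.
2. Record the time of the eligibility decision and the time of allocation in the case report form.
3. State that no exclusion under 2.1 of the criteria list removes a patient once allocated, and that every allocated patient stays in the intention-to-treat set and is followed.
4. Count failure to pass or complete the allocated device as stapler dysfunction (secondary outcome 3), not as ineligibility.
5. State in advance how allocated patients without an anastomosis enter the leak endpoint, with a sensitivity analysis under the alternative handling, because counting them as non-leaks can favour noninferiority.

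The cost is protocol wording and two time stamps, plus a few allocated patients without a stapled anastomosis who remain in the analysis set. If the sponsor instead chose to reconcile the sections by changing the operative sequence, that would be a clinical decision and more than a wording change.

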##### Laparoscopic approach

2.3.3.2

Following trocar installation and examination of abdominal cavity and pelvic cavities, para-aortic lymph node dissection is performed with the skeletonization of the inferior mesenteric artery and preservation of the integrity of the preaortic and prehypogastric plexuses. The inferior mesenteric artery is divided below the origin of the left colic artery; the latter is preserved. The sigmoid colon and the distal portion of the descending colon are mobilized in the medial-lateral direction. The inferior mesenteric vein is cut at the level of the upper edge of the body of the pancreas. After that, a TME is performed with the preservation of the hypogastric nerves and pelvic nerve plexuses. The rectum is transected with a linear cutter stapler at least 2 cm below the inferior margin of the tumor. A mini-laparotomy is performed. In the wound, the separated rectum and the sigmoid colon are removed, the mesentery of the sigmoid colon is transected in the direction of the transection of the intestinal wall. Sigmoid colon is divided and the circular stapler anvil is fixed in its stump with a purse-string suture. The stump of the intestine with circular suturing device anvil is immersed in the abdominal cavity, the laparotomy wound is sutured. A repeated laparoscopy is performed. From the side of the perineum, after preliminary washing of the rectal stump, the surgeon inserts the circular suturing device into the anal canal. Under guidance with a laparoscope, the trunk of the working part of the apparatus is pierced in the area on one of the edges of the suture line of the rectal stump. The sigmoid colon stump is moved to the pelvic cavity, the rod of the device head is inserted into the trunk of the operating part, an end-to-end colorectal anastomosis is secured. The height of the anastomosis is measured in centimeter from the anal verge. After the removal of the circular suturing device, the integrity of the resected intestinal rings is assured. The suture line is tested for leakage. A transanal silicone tube is installed. A preventive transverse colostomy is formed. A silicone drain tube is installed in the pelvic cavity. Abdominal wall openings are sutured. Sterile dressings are applied.

#### Early postoperative period

2.3.4

It is defined as the time period from the completion of the surgery and up to 30 days after the surgery. The patient is extubated after return of consciousness, reflexes and muscle tone, either in the operating room, or the intensive care unit (ICU). If necessary, the patient may require a prolonged mechanical ventilation. In the ICU, vital functions are monitored, with a special attention paid to the drainage discharge and the state of postoperative dressings. An individual anesthesia regimen is selected, which may include NSAIDs, opioid pain relievers, and regional block anesthesia. Laboratory tests (usually twice a day, more often if necessary), correction of electrolyte imbalance, prokinetic agents, prevention of thromboembolic complications, antibiotics and PPIs are mandatory. Intake of colorless liquid is permitted from the 1st hours after surgery, the volume of liquid consumed per day depends on time of return of bowel function and the extent of the surgery. Parenteral nutrition may be prescribed if the absence of enteral nutrition within 72 hours is expected, or due to baseline protein-energy malnutrition. The treatment is also adjusted to the existing comorbidities.

Patient ambulation occurs on the 1st day, routinely in the morning of the next day postsurgery. The patient is put into upright position without sitting down. Upon compensation of the vital functions and the absence of foreseen complications of nonsurgical nature, the patient is transferred from the ICU to ward, where urinary catheter is removed.

#### Late postoperative period

2.3.5

It is defined as the time period starting at 31st day postsurgery. At weeks 4 to 6, according to the standard protocol, the preventive stoma is closed. Also, the patient is asked to fill out the questionnaire forms SF-36, QLQ-C30, LARS, and CCIS to assess the changes in the quality of life of the patient relative to the baseline level.

Following discharge, all subjects will be required to provide 4 filled out questionnaires (SF-36, QLQ-C30, CCIS, LARS), and report their pain level using the VAS. To ensure patient compliance to protocol requirements, all subjects will be notified telephonically and/or via e-mail. If the patient is unavailable, he or she must be contacted at least 3 times within the follow-up timeframe, before considered dropped-out from the study.

All subjects are strongly advised to adhere to bland diet, and are recommended to abstain from the intake of meat and fatty meals within at least 1 month after stoma reversal. Patients are also advised to minimize the intake of NSAIDs in the absence of comorbidities requiring NSAID treatment. NOAC administration is necessary during the 1st week after surgery to minimize the risk of thrombosis.

### Outcomes

2.4

#### Primary outcome measure

2.4.1

The primary outcome measure is the difference between the 2 groups in the incidence of colorectal anastomosis leakage documented with an X-ray and/or CT scan in the time period between the LAR and stoma reversal surgery.

As proposed by the International Study Group of Rectal Cancer, AL is defined as a “defect of the intestinal wall integrity at the colorectal or coloanal anastomotic site (including suture and staple lines of neorectal reservoirs) leading to a communication between the intra- and extraluminal compartments,” or presence of “a pelvic abscess close to the anastomosis.”^[14]^ In context of primary outcome analysis only presence or absence of diagnosed AL (dichotomous aggregation method) from the day of intervention to preventive stoma reversal will be considered. The timeframe for the primary outcome measure is defined as the period between the initial surgery and stoma reversal, which usually takes place at 4 to 6 weeks after LAR, and may differ significantly between subjects due to variability of AL presentation and symptoms. Additionally, AL may be asymptomatic and discoverable only with imaging studies, which are only necessary to ensure the safety of stoma reversal surgery.

All patients undergoing LAR with stapled colorectal anastomosis formation will be treated according to intervention protocol described in the corresponding section. The patients’ status will be monitored twice a day during rounds. AL has a multifaceted clinical course and has no pathognomonic features; it may be asymptomatic and require no intervention, or it can lead to serious complications, such as peritonitis and sepsis. The clinical signs of AL include the following:

1.General1.1. Fever (≥38.0°C)1.2. Tachycardia (≥100/min)1.3. Increased respiratory rate (≥30/min)1.4. Renal insufficiency (<30 mL/h or <700 mL/d)1.5. Altered mental status (agitation/lethargy, GCS < 15)1.6. Deterioration of overall clinical condition1.7. Peritonitis (clinical signs of abdominal guarding, rebound tenderness, abdominal pain worsening with movement, etc)1.8. Sepsis (qSOFA ≥ 2)2.Local2.1. Bowel obstruction2.2. Abnormal drain content (purulent/turbid/air)2.3. Purulent or fecal vaginal discharge (rectovaginal fistula)2.4. Abdominal pain other than wound pain2.5. Fascial dehiscence3.Laboratory signs include:3.1. Leukocytosis3.2. C-reactive protein elevation

There are several ways in which AL can be diagnosed in the investigated subjects (Fig. 1).

1.If any of these clinical signs prompting the attending surgeon to suspect AL are present, the patient will undergo imaging studies for further evaluation. If there is no evidence of nonanastomotic complications, an X-ray with contrast enema will be performed. In presence of any clinical signs of nonanastomotic complications (pancreatitis, pneumonia, etc), a CT scan of the chest, abdomen, and pelvis with contrast enema will be obtained to simultaneously exclude anastomosis-unrelated postoperative complications. If CT results suggest AL, the patient will reach the primary endpoint, and will be treated accordingly to their condition. Further treatment will not be discussed in this protocol as it is irrelevant to endpoint analysis.2.If there are no symptoms suggesting AL before discharge, the subject will undergo X-ray with contrast enema as a part of preoperative assessment prior to stoma reversal procedure in 4 to 6 weeks after the initial surgery according to the standard protocol implemented at the study center. If the X-ray findings suggest AL, the subject will reach the primary endpoint.

